## Abstract

**Background:**

As intensive care mortality is high, end of life is a subject of major concern for intensivists. In this context, relatives are particularly vulnerable and prone to post-ICU syndrome, in the form of high levels of anxiety, depression, post-traumatic stress, and complicated grief. Grieving families suffer from a feeling of abandonment and evoke the need to get back in touch with the team to ask questions and remove doubts, but very few actually do. Aiding families during the grieving process is an important aspect of palliative care. A condolence letter represents an opportunity to recognize the pain of the family member and the strong tie that linked the family member to the ICU team, and to offer additional information if necessary. The goal of the study is to measure the impact of the condolence letter on the experience of bereaved families after a death in the ICU. Our hypothesis is that a post-death follow-up in the form of a condolence letter sent by the ICU physician who was in charge of the patient may help to reduce the risks of presenting symptoms of anxiety/depression, post-traumatic stress, and complicated grief.

**Methods/design:**

This is a randomized, controlled, multicenter study. Research will compare two groups of bereaved family members: one group that does not receive a condolence letter (control) and one group that receives a condolence letter 15 days after the death (intervention). Each of the 22 participating centers will include 12 relatives. Participating relatives will be followed up by phone with a call at 1 month and one at 6 months to complete questionnaires, permitting evaluation of post-ICU burden. The main outcome is anxiety and depression measured at 1 month. Other outcomes include evaluation of quality of dying and death, post-traumatic stress, and complicated grief.

**Discussion:**

This study will allow us to assess if sending a condolence letter can reduce the risks of presenting symptoms of anxiety and depression, complicated grief, and symptoms of post-traumatic stress disorder after the death of a loved one in the ICU.

**Trial registration:**

Clinical Trials registration number: Clinicaltrials.gov NCT02325297 (23 December 2014).

**Electronic supplementary material:**

The online version of this article (doi:10.1186/s13063-016-1212-9) contains supplementary material, which is available to authorized users.

## Background

### Context

As ICU mortality is high, end of life is a subject of major concern for intensivists. With a mortality rate of 20 % [1], end-of-life care has become a daily responsibility. Many deaths follow a decision to withhold or withdraw treatment, situations where physicians, nurses, and relatives must work together towards the most consensual decision. In the ICU, relatives are no longer simple visitors: they play active roles both at the patient’s bedside and with the team, thus creating a complex and unprecedented experience. A recent qualitative study showed that, after the loss, grieving families suffer from a feeling of abandonment by the ICU team [2]: “*During the end-of-life process you are cared for and then they sort of drop you*”. Indeed, the way families are cared for in the ICU is “intense”: daily contact with the nursing staff and physicians, precise information, phone calls, units that are open 24 hours a day. When the patient dies, families do not always have the opportunity to say goodbye to the team that cared for the patient, no longer receive attention from them, and therefore feel abandoned. Furthermore, for many family members, a few months after the death questions surface, incomprehension arises, doubts accumulate, and these questions remain without answer, provoking significant suffering and sometimes guilt. Many families evoke the need to get back in touch with the team to ask questions and remove doubts so as to ease the grieving process, but very few actually do.

A recent study from the Famiréa research group [3] shows that after the death of the patient in the ICU 52 % of family members present complicated grief symptoms at 6 months and 53 % at 12 months (using the ICG scale [4]) as well as a high risk of presenting post-traumatic stress symptoms (43.6 % at 6 months and 36.2 % at 12 months). The follow-up offered by the study (phone calls) was received as real support by the majority of families, a way of feeling not abandoned, the feeling that their pain counted, and that the ICU team continued to worry about them [2]. The Famiréa research group received numerous thank you letters. This brought us to consider the question of post-death follow-up and the interest of sending grieving family members a condolence letter.

### Condolence letters, a rare practice

Literature on follow-up with grieving families essentially concerns deaths in oncology units and in hospice care. These studies focus above all on the follow-up practices of oncology and hospice care physicians for grieving families: participation in rituals (funerals, for example), home visits, phone calls or condolence letters. Three studies [5–7] highlight heterogeneous and also very unpredictable practices: condolence letters written in 30–70 % of cases, few phone calls, little participation in grieving rituals. These three studies also highlight the barriers to condolence practices: lack of time or resources, the importance of maintaining professional distance, fear of professional burn-out, the difficulty of identifying which family member to contact, and, finally, the lack of recommendations for writing condolence letters. A literature review on the subject of interventions proposed to bereaved families demonstrates that many interventions are tested (from grief support groups to drug treatments to psychotherapy) without significant conclusions and that the majority of these studies suffer from significant methodological weaknesses [8]. Some studies ask the question of the identity of the person who could participate in the follow-up of grieving families: most often the doctor is cited and sometimes the nurse [9].

It is interesting to note that most studies focus on the practices of clinicians (oncologists and hospice care), but no study measures precisely the impact of these strategies on grieving individuals themselves. Two studies address this point, without it being the subject of the study, and demonstrate that a good interaction with the referring doctor of the dying patient, before and after his death, reduces complications in the grieving process [10] and, in the case of a phone call, diminishes the feelings of abandonment and solitude of family members [11]. Caring for family members after the death of a patient is one of the pillars of a good palliative approach. In its *Clinical Practice Guidelines for Quality Palliative Care*, the National Consensus Project for Quality Palliative Care [12] puts forward that among the nine points defining palliative care, one is dedicated to aiding families during their loved one’s illness and after death, during the grieving process. In the practical recommendation section on psychological care of patients and families, one section is dedicated to post-death follow-up and aiding grieving families during the first year of bereavement: after the patient’s death, family members may need help and follow-up allows them to be referred to professionals, if that is judged necessary, allows their pain to be recognized, and allows them to express themselves and to get back in touch with the care team if necessary. Therefore, contact with bereaved family members in the form of a condolence letter could be part of the care recommended by these guidelines.

### Condolence letter, whose responsibility?

The question of the physician’s responsibility is posed: When does the physician’s responsibility to his patient end? When the patient dies? Doesn’t care of the family constitute part of the physician’s responsibility to his patient? This reflection has fed some debates and publications, notably in the *New England Journal of Medicine* [13] and *Chest* [14]. Throughout these papers, a consensus appears: care doesn’t end at the death of the patient; it continues beyond with a last act of care, notably in the form of a condolence letter. “*A physician’s responsibility for the care of a patient does not end when the patient dies. There is one final responsibility — to help the bereaved family members. A letter of condolence can contribute to the healing of a bereaved family and help achieve closure in the relationship between the physician and the patient’s family*” [13]. The condolence letter not only allows family members to feel recognized and comforted but it also allows the caregiver who writes it to express his feelings and bring closure to a relationship. Finally, the practice of writing a condolence letter allows hospital units to orient their unit’s culture towards a more humanist approach to care and to paying attention to details in the relationship with the patient, the patient’s family, or even between the family and the patient: this is important for training young physicians and young nurses. Therefore, the condolence letter can be seen as a “*professional responsibility of the past that is important to revive*” [13].

### Recommendations

The literature allows us to better understand how to construct a condolence letter. Several points should be highlighted [13, 15]: the condolence letter should be short and handwritten; it should recognize the death and the pain of the loved one and bring him comfort; it should refer to the patient, or, if the physician didn’t know the patient well, to what the loved one did for the patient during his hospitalization (for example, his presence, participation in the care); there should be a reminder that the medical team remains available to answer questions and give the contact information of the referring physician; finally, the physician closes the letter with the presentation of his condolences, without being too formal: a “personal touch” is recommended.

The condolence letter, an obsolete practice these days in most medical specialties, appears to be the object of renewed interest. It is recommended both for bereaved family members and for the medical care team.

### Justification of the research project

To the best of our knowledge, there are no published studies that make reference to condolence letters (or any other practice used to follow up with bereaved family members) in the context of the ICU. Yet many studies have demonstrated the fragility of family members during the patient’s stay in the ICU and after discharge, notably if the patient dies. During the patient’s stay family members suffer from symptoms of anxiety and depression [16] as well as difficulty in understanding medical information [17].

The impact of the ICU stay on family members is real and long-lasting; a multicenter study done on 284 family members three months after the discharge or death of the patient demonstrates an important risk for family members. In fact, one-third of families show symptoms of post-traumatic stress disorder (PTSD). The predictive factors are [18] the quality of the information (the more the family members are dissatisfied, the greater the risk that they will present PTSD symptoms), and the death of the patient (the more the families feel they were implicated in the decision-making process for their loved one, the higher the risk of presenting symptoms of PTSD).

Strategies have been tested to reduce these long-term consequences, notably an end-of-life family conference that improves the experience of bereaved family members by reducing the risk of presenting PTSD 3 months after the patient’s death [19].

Finally, studies show on the one hand a higher risk of complications in the grieving process and a significant risk of PTSD and on the other hand that bereaved family members in this context need help, need to be recognized, need to be supported during their bereavement. A strategy must be developed to recognize both the pain of the family member and the strong tie that linked the family member to the ICU team.

### Objectives

The goal of the study is to measure the impact of the condolence letter on the experience of bereaved families after a death in the ICU: Does the condolence letter to bereaved family members reduce their risk of presenting symptoms of anxiety and depression and, later, symptoms of PTSD and complicated grief?

#### Hypothesis

Post-death follow-up in the form of a condolence letter sent by the intensive care physician who was in charge of the patient’s care may help to reduce the risks of presenting symptoms of anxiety/depression, post-traumatic stress, and complicated grief.

## Methods and design

### Population

Bereaved family members after the death of an adult patient in the ICU, fulfilling all inclusion criteria and none of the exclusion criteria.

Inclusion criteriaDeath of an adult (age ≥18) patientDeath of a patient whose family has met the ICU team at least once before the deathAn ICU stay of at least two days

Non-inclusion criteriaDeath of a pregnant womanFamily member who doesn’t speak FrenchRefusal of the family member

As in previous Famiréa studies, only one family member is included: the “family representative,” that is, the designated health care proxy and, in his (her) absence, the family member most involved in the relationship with the ICU team, or by default the spouse (or partner), then the parents or children of the patient, then another member of the family.

### Methodology

This is a randomized, controlled, multicenter study. Research will compare two groups of bereaved family members: one group that does not receive a condolence letter and one group that receives a condolence letter 15 days after the death. Randomization will be stratified by center and balanced by permutation blocks (the size of which will not be communicated to the investigators). It will be done via a web server on a secure connection and will occur at inclusion (in the 24 hours following the death of the patient).

Family members will be included the day of the patient’s death (consent). The randomization (allowing the identification of family members of deceased patients who will receive a condolence letter) will occur after the consent by the family member to participate in the study—in the 24 hours following the death of the patient.

#### Primary endpoint

The HADS scale (Hospital Anxiety and Depression Scale) — 1 month after the death of the patient.

#### Secondary endpoints

HADS scale at 6 months after the death of the patientCAESAR scale measuring the experience of the end-of-life in the ICU — 1 month after the patient’s deathIES-R (Impact of Event Scale, Revised) measuring the risk of presenting symptoms of post-traumatic stress — 6 months after the death of the patientICG (Inventory of Complicated Grief) measuring the risk of presenting complicated grief symptoms — 6 months after the death of the patientFeasibility questionnaire for doctors who have written a condolence letter (Fig. 1)

**Fig. 1 Fig1:**
[figure not shown]
Study design

#### Design

At the time of the patient’s death, the information letter (see Additional file 1) is given to the family member and consent to participate will be obtained. The same letter will be given to the two groups of family members; for ethical and psychological reasons, the condolence letter is not mentioned in the information letter. Once consent is obtained, relatives will be randomized to the intervention or the control group. For all the included patients, the physician will complete a “patient characteristics form.”

Control standard of care: no condolence letters to patients’ relativesAll follow-up calls will be blinded: the caller will not know whether or not the family member received a condolence letter.Day 30: Call to the family member by the Famiréa group 1 month after the death to complete the HADS and the CAESAR scale.Day 180: Call to the family member by the Famiréa group 6 months after the death to complete the HADS, the ICG, and the IES-R.

Intervention: sending a condolence letter to patients’ relativesDay 1: in the 24 hours following the death, the physician in charge of the patient will write, with the help of the patient’s nurse, a condolence letter: it will be handwritten and written according to the recommendations of the group Famiréa. It will integrate the five following domains: 1) recognize the death and name the deceased; 2) mention the deceased; 3) recognize the family member; 4) offer help; 5) express sympathy (see Additional file 2). The letter will be photocopied and the original will be put in an envelope on which the family member’s address will be handwritten. The envelope will be placed in the physician’s office until it is sent via the post office. The photocopy of the letter will be placed in the case report form.

Following the writing of the letter, the physician will complete a questionnaire about the writing process (length of time, difficulties encountered, emotions).Day 15: The letter will be sent (in a hand-addressed envelope). An automatic alert (by email) generated by the randomization software will remind the physician to mail the condolence letter.Day 30: Call to the family member by the Famiréa group 1 month after the death to complete the HADS and the CAESAR scale.Day 180: Call to the family member by the group Famiréa 6 months after the death to complete the HADS, the ICG, and the IES-R.

In both the control and intervention groups, the reactions of the family member following the death of the patient will be screened. Did the family member call the physician? Did he (she) write to the team? Did he (she) come back to the unit? The screening will be done for 4 months following the death of the patient. Any letters written to the teams by the families during this period will be photocopied and sent to the Famiréa group.

### Data analysis

The analysis will be done according to the intention-to-treat principle (that is, each subject will be analyzed in the intervention group to which he (she) was assigned by the randomization, regardless of whether or not it was effectively done). We will report, in each randomization group, summary statistics according to the data (median and interquartile range, percentage with a 95 % confidence interval).

The proportion of family members with symptoms of anxiety/depression at days 30 and 180 will be compared between randomization arms by an exact Fisher test. A comparison of the HADS score distribution will be done using a non-parametric Wilcoxon rank sum test.

A regression model will be used later to search for associated factors should anxiety or depressive syndromes occur, or interactions between intervention effect and family member characteristics, notably the relationship (spouse, child) age, way of life.

Text data will also be analyzed with descriptive methods (factorial analysis of correspondences, word cloud), then predictive methods (text mining).

Statistical analysis will be done on software from SAS (SAS Inc., Cary, NC) and R (http://www.R-project.org/). All the tests will be two-sided with *p*-values of 0.05 or less indicating statistical significance.

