### Justification of the sample size

On the basis of a previous Famiréa study [18], our hypothesis is that receiving a condolence letter could reduce the risk of presenting symptoms of anxiety/depression (HADS score) by 30 %, diminishing the prevalence at 1 month from 60 % in the group without a condolence letter to 42 % in the group with a condolence letter. In order to detect such a difference between the two groups, with a type I error of 0.05 and a power of 0.80, it is necessary to include 240 family members (120 in each group), that is, 12 inclusions per center in the 22 participating centers (see Additional file 3).

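### The Data analysis section names only arm-wise confidence intervals and p-values, and no between-arm effect with its uncertainty, although the trial is sized on one

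*Protocol article*

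**What the plan says.** The Objectives section of the protocol article states: "The goal of the study is to measure the impact of the condolence letter". The Justification of the sample size section makes this a between-arm quantity. Its premise reads: "our hypothesis is that receiving a condolence letter could reduce the risk of presenting symptoms of anxiety/depression". The relative reduction assumed there is 30 %, and the section spells it out in absolute terms as follows: "diminishing the prevalence at 1 month from 60 % in the group without a condolence letter to 42 % in the group with a condolence letter".

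The Data analysis section then fixes the outputs:

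- **Description.** "We will report, in each randomization group, summary statistics according to the data", namely medians with interquartile ranges, and percentages with a 95 % confidence interval. This is the only confidence interval the article mentions.
- **Comparison.** A Fisher exact test for the proportions at days 30 and 180, and a Wilcoxon rank sum test for the HADS score, all two-sided and read against a p-value of 0.05 or less.
- **Regression.** A later model to look for associated factors and for interactions with the intervention effect. It is not presented as the estimate of the letter's effect.

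The Methodology section states that randomization is stratified by center. Neither named test uses the centers.

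**The concern.** The aim and the sample size concern a difference between arms. The named intervals concern each arm separately, and the named comparisons, as described, yield p-values. The quantity that the trial was built to detect is therefore not among the specified outputs together with its precision.

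This matters most if the result is not significant. A p-value above 0.05 does not tell the reader whether an 18-point benefit has been ruled out, or whether a harm remains possible. Harm is a fair question here because the tests are two-sided. It matters after a positive result too: the Discussion foresees extending the practice to all ICUs, and that decision needs the size and precision of the effect. Arm-wise intervals are a poor substitute, because they can overlap when the difference is significant.

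**Working it through.** **Inputs.** From Justification of the sample size: 60 % v 42 %, "with a type I error of 0.05 and a power of 0.80", 120 per group. From Data analysis: two-sided tests. The event counts below are assumed examples at 120 per arm; the article gives no results.

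**1. The plan's own figure.** With pooled variance, no continuity correction and mean proportion 0.51:

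n per arm = [1.96 × √(2 × 0.51 × 0.49) + 0.842 × √(0.60 × 0.40 + 0.42 × 0.58)]² / 0.18² = 119.9, so 120 per arm and 240 in total.

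The stated size is reproduced (power 0.800). The planned effect is 60 − 42 = 18 points, or a risk ratio of 42/60 = 0.70.

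**2. Precision of an arm and of the difference.** At the planned rates:

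- Control arm: 1.96 × √(0.60 × 0.40/120) = 8.8 points.
- Intervention arm: 1.96 × √(0.42 × 0.58/120) = 8.8 points.
- Difference: 1.96 × √(0.24/120 + 0.2436/120) = 1.96 × 0.0635 = 12.4 points.

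If exactly 60 % v 42 % is observed, the difference is 18.0 points (5.6 to 30.4) and the risk ratio 0.70 (0.54 to 0.90).

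**3. Assumed results, control v letter, 120 per arm.** Difference d = p₁ − p₂, with Wald interval d ± 1.96 × √(p₁(1−p₁)/120 + p₂(1−p₂)/120). A positive value favors the letter.

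| Events | Fisher p | Difference, points (95 % CI) | Are 18 points excluded? |
|---|---|---|---|
| 72 v 55 | 0.038 | 14.2 (1.7 to 26.7) | no |
| 72 v 60 | 0.15 | 10.0 (-2.5 to 22.5) | no |
| 72 v 66 | 0.51 | 5.0 (-7.5 to 17.5) | yes, narrowly |

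For example, 72 v 60: d = 0.600 − 0.500 = 0.100; standard error = √(0.24/120 + 0.25/120) = 0.0639; 1.96 × 0.0639 = 0.125.

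- In the first row the arm intervals overlap (51.2 to 68.8 % and 36.9 to 54.7 %) although the test is significant.
- The second and third rows would both be reported as non-significant. One leaves the planned benefit open and the other just excludes it. Neither excludes some harm (up to 2.5 and 7.5 points).

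**4. Can test and interval disagree?** Yes. For 72 v 56, Fisher's p is 0.052, while the Wald interval for the difference is 0.8 to 25.8 points and excludes zero. If an interval is added, the test should be chosen to go with it.

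**The case against.** The strongest reply is that this is a gap in a condensed article and not an error. A fuller analysis plan may name the effect measure, nothing says the listed outputs are exhaustive, and a percentage with its interval is a valid description of an arm. The text never proposes to judge the difference by comparing arm intervals. The later regression also refers to an intervention effect.

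Much of this stands. A reader might infer that the trial never estimates its effect, or that a null result could not be interpreted. The article does not support either reading. The two arm percentages give the point estimate of both the difference and the ratio. With the denominators, anyone can derive an unstratified interval. The arm intervals even combine to it: for 72 v 66 the half-widths are 8.77 and 8.90 points, and √(8.77² + 8.90²) = 12.5. Arm-wise intervals need not be dropped.

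What the reply does not remove is that the section is not merely silent. It decides where the confidence intervals go and which tests decide the comparison, and it places the intervals on the arms and leaves center out of the tests. The regression is for later exploration and is not offered as the primary estimate. An analysis plan that we cannot see may well settle this, but the choice as stated is still the weaker one.

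**Conclusion.** The concern holds in a limited form. As stated, the analysis names arm-wise intervals and p-values from unstratified tests, and specifies no between-arm effect with its uncertainty. This sits badly with an aim of measuring impact, a sample size built on an 18-point (30 % relative) reduction, and randomization within center. The information is recoverable from the arm counts, so the defect lies in what is designated as the result, not in what the data can show.

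The size of the issue is the width of the missing interval: about ±12.4 points at the planned rates with 120 per arm, against a planned effect of 18. That is wide enough for two non-significant results to mean different things, as 72 v 60 and 72 v 66 show. These figures assume 120 analyzed per arm, the example counts, and unstratified Wald intervals; a center-stratified interval would differ somewhat. It is a worthwhile correction, but it leaves the design and the data collection as they are.

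**What to change.** In Data analysis, state that the primary result is the day-30 risk difference stratified by center (Mantel-Haenszel), together with the risk ratio, each with a 95 % CI. Read both against the planned 18 points and 30 % relative reduction, and say whether harm is excluded. Take the primary p-value from the matching center-stratified test, so that test and interval agree. With about 12 relatives per center, use a variance formula that remains valid with many small strata. For the HADS score, add a location shift (Hodges-Lehmann) with a 95 % CI. The arm-wise percentages and their intervals can stay as description.

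The cost is a few sentences and slightly more analysis work on the same data. There is one small downside: the primary test would no longer be the stated Fisher test. The change should therefore be documented before the allocation is revealed to the analysts. The sample size does not change.

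### The exact Fisher test for the binary HADS endpoint is conservative: its own discreteness costs about 4 points of power at 240 relatives, and ignoring the center stratification can cost up to about 4 more if centers differ.

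*Protocol article*

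**What the plan says.** The Methodology section of the protocol article fixes the allocation: "Randomization will be stratified by center and balanced by permutation blocks". The Data analysis section says that the proportion of relatives with symptoms at days 30 and 180 "will be compared between randomization arms by an exact Fisher test". Center plays no part in that test. The only model mentioned is exploratory and comes afterwards ("A regression model will be used later to search for associated factors"), and center is not among the characteristics listed for it.

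The section Justification of the sample size plans for a fall in prevalence "from 60 % in the group without a condolence letter to 42 % in the group with a condolence letter", "with a type I error of 0.05 and a power of 0.80", and arrives at 240 relatives, 120 per group. It equates this with "12 inclusions per center in the 22 participating centers". That product is 12 × 22 = 264, so both totals are examined below.

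**The concern.** Balancing the groups within each center removes between-center variation from the treatment contrast. An unstratified test still counts that variation in its reference variance. If centers differ in outcome, the true type I error then drops below 5% and power is lost. Fisher's exact test adds a conservatism of its own, because its attainable p-values are discrete; this occurs even if all centers are identical.

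The test is named in the article, so this is a stated choice and not a detail left to a fuller plan. What is at stake is sensitivity: the named test may not reach the stated power at the stated sample size, although a test that follows the design would reach or nearly reach it.

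**Working it through.** **Inputs from the article:** rates 0.60 and 0.42; two-sided alpha 0.05; power 0.80; 120 per group (240), or 22 × 12 = 264 (132 per group); stratification by center.

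**Assumed:** the between-center variation, for which the article gives no figure. It is modeled as a normal center effect on the logit scale with variance s², giving a latent ICC = s²/(s² + π²/3), varied from 0 to 0.15. Latent values of 0.05 and 0.10 correspond to about 0.04 and 0.08 on the probability scale.

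**Step 1: reproduce the plan's figure.** Pooled-variance formula, no continuity correction, mean rate 0.51:

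n = [1.96·√(2·0.51·0.49) + 0.842·√(0.60·0.40 + 0.42·0.58)]² / 0.18²
= [1.386 + 0.585]² / 0.0324 ≈ 119.9, so 120 per group.

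The 240 reproduces. The formula is that of an unstratified, uncorrected chi-square test. It contains neither center nor Fisher's test. With a continuity correction, which approximates Fisher's test, it gives 131 per group.

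**Step 2: exact behavior of Fisher's test, no center effect.** Summing both binomial distributions over all tables with two-sided p ≤ 0.05:

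- 120 per group: power 0.750, size 0.039 at a common rate of 60%. Pearson chi-square: power 0.790, size 0.053.
- 132 per group: power 0.818, size 0.038. Pearson: power 0.849, size 0.051.

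Discreteness alone therefore costs 0.790 − 0.750 = 4 points at 240 and 0.849 − 0.818 = 3 points at 264.

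**Step 3: add center effects.** Simulation with 6 relatives per arm per center, 20 centers (240) or 22 centers (264), marginal rates held at 60% and 42% (60% in both arms for size), 100,000 to 150,000 runs per setting. Cochran-Mantel-Haenszel (CMH) statistic: |Σ(x₁ₖ − n₁ₖtₖ/Nₖ)| / √Σ[n₁ₖn₂ₖtₖ(Nₖ − tₖ)/(Nₖ²(Nₖ − 1))], compared with 1.96, no continuity correction. Pearson's test is included to separate the two sources of loss.

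| Total | Latent ICC | Size: Fisher / Pearson / CMH | Power: Fisher / Pearson / CMH | Exact-test part (Pearson − Fisher), points | Center part (CMH − Pearson), points |
|---|---|---|---|---|---|
| 240 | 0 | 0.039 / 0.053 / 0.051 | 0.752 / 0.791 / 0.796 | 3.9 | +0.5 |
| 240 | 0.05 | 0.035 / 0.047 / 0.050 | 0.757 / 0.797 / 0.818 | 4.0 | +2.1 |
| 240 | 0.10 | 0.031 / 0.042 / 0.049 | 0.762 / 0.800 / 0.831 | 3.9 | +3.1 |
| 240 | 0.15 | 0.027 / 0.038 / 0.050 | 0.768 / 0.807 / 0.844 | 3.9 | +3.7 |
| 264 | 0 | 0.039 / 0.052 / 0.051 | 0.818 / 0.849 / 0.837 | 3.1 | −1.2 |
| 264 | 0.05 | 0.035 / 0.047 / 0.050 | 0.822 / 0.853 / 0.852 | 3.2 | −0.1 |
| 264 | 0.10 | 0.032 / 0.044 / 0.050 | 0.830 / 0.860 / 0.865 | 3.0 | +0.5 |
| 264 | 0.15 | 0.028 / 0.040 / 0.050 | 0.831 / 0.862 / 0.876 | 3.1 | +1.4 |

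**Step 4: sensitivity to the layout.** With 240 relatives spread at random over 22 centers in blocks of 4 (block size assumed; 40,000 runs), group sizes are no longer exactly equal and Fisher's test is a little less discrete. For latent ICC 0 to 0.10, power is 0.765 to 0.774 for Fisher, 0.792 to 0.801 for Pearson and 0.797 to 0.825 for CMH. The exact-test part is then about 3 points and the center part 0.5 to 2.4 points. The direction is unchanged.

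**Step 5: continuity correction.** A continuity-corrected CMH test has power of only 0.758 at 240 with ICC 0, and size 0.037. The correction gives the gain back.

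**The case against.** The strongest reply is that nothing here is invalid. A conservative test does not inflate false positives, the planned 240 never counted on a gain from stratification, and at 264 analyzed relatives Fisher's test already exceeds 0.80. All of this stands, and it limits the point to efficiency.

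Several stronger readings are tempting but are not supported:

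- *The whole loss comes from ignoring center.* It does not. With identical centers, Fisher's test is already 4 points below Pearson's at 240. The center part is smaller in most settings, depends on an ICC that the article does not give, and at 264 is nil or slightly negative up to a latent ICC of 0.05.
- *The score comparison should be stratified too.* The article says: "A comparison of the HADS score distribution will be done using a non-parametric Wilcoxon rank sum test". In a simulation of a 0–42 score (2,000 runs, Monte Carlo error about 1 point), the center-stratified van Elteren test lost about 1 to 3 points against the plain Wilcoxon test at ICCs up to 0.05 and gained about a point only at 0.10 with even recruitment. No calculation supports replacing it.
- *No between-group interval will be reported.* The article promises summaries per group ("We will report, in each randomization group, summary statistics according to the data") but does not rule out a between-group estimate. A condensed article may leave that to the full plan.
- *Relationship and age should enter the main analysis.* An unadjusted primary comparison is legitimate in a randomized trial; adjustment is a preference.

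**Conclusion.** The point holds as a modest efficiency point about the binary HADS comparison. At exactly 120 per group, the named test has power 0.75 where the plan states 0.80. That statement needs no assumption beyond the article's own rates. Stratifying by center and leaving the exact test together gain about 4.5 to 7.6 points at 240 (0.752 to 0.796 at ICC 0; 0.768 to 0.844 at ICC 0.15) and about 2 to 4.5 points at 264. The fall in Fisher's size to about 0.03, and the share of the gain credited to center, rest on the assumed latent ICC of up to 0.15 and on near-even recruitment across centers. If centers do not differ, the center share is close to zero at 240 and about −1 point at 264. The planned tests remain valid, and the trial's conclusions are not at risk of bias from this choice.

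**What to change.** In Data analysis, replace the exact Fisher test for the proportion with anxiety/depression symptoms at days 30 and 180 by the Cochran-Mantel-Haenszel test stratified by center. State that no continuity correction is used and check the software setting for it. Report the common risk difference across centers with its 95% confidence interval. Leave the Wilcoxon test as it is.

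The cost is a change of wording and a few lines of SAS or R. Center is already recorded as the randomization stratum, so no new data are needed. The change should be fixed before any comparison by group is seen.

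The downside is that the test is asymptotic with small strata (about 12 relatives per center) and can lose about a point against an unstratified chi-square test if centers do not differ. In the simulations above its size stayed between 0.049 and 0.051, so the small strata did not harm error control in those layouts.
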